
### Between follow-up sessions

For the first 20 weeks, GRA2 will call the Exercise Group participants every two weeks to monitor their safety, adherence, and progress using a short, structured phone survey. The results of the phone survey will be used to guide the adjustments/progression of the structured exercise and step counts protocols. After 20 weeks, GRA2 will conduct the phone survey every four weeks. In addition, the participants will return their exercise daily logs every four weeks.

#### Follow-up sessions

GRA1 will schedule follow-up sessions for all participants at 3, 6, 9, and 12 months after ADT initiation. Primary outcome (HRQOL and physical function) and secondary outcome variables (physical fitness, psychosocial-cognitive functions, and physical activity) will be re-assessed during the follow-up sessions.

#### Data collection

At baseline session, GRA1 will collect independent variables of socio-demographic, clinical, and behavioral factors using a structured assessment questionnaire. Socio-demographic factors will include (1) age, (2) marital status, (3) ethnicity, (4) living arrangement, (5) education, (6) work status, (7) alcohol consumption history, and (8) smoking history. Clinical factors will include (9) current cancer stage, (10) time since diagnosis, (11) treatment intent (i.e., curative vs. palliative). Other baseline data including testosterone level, Gleason score, and comorbidities will be obtained from the medical records.

At baseline and 12-months after ADT initiation, GRA1 will obtain bone mineral density (for *bone health *as part of the primary outcomes) of the lumbar spine, hip and whole body and body composition (for *physical fitness *as part of the secondary outcomes) of the whole body from the dual-energy x-ray absorptiometry (DXA),^a ^and PSA level from the medical records.

At baseline and all follow-up sessions (3, 6, 9, and 12 months), the rest of the primary (HRQOL and physical function) and secondary outcome variables (physical fitness, psychosocial-cognitive functions, and physical activity) will be assessed. *HRQOL *will be assessed using (1) the Functional Assessment of Cancer Therapy Prostate Module (FACT-P) [25] as a disease-specific instrument, and (2) the Medical Outcomes Study 36-item Short Form Health Survey Version 2 (SF-36v2) [26] as generic instrument that is chosen for its depth of coverage, breadth of domains, and widespread use in medical outcomes assessment. *Physical function *will be assessed using (3) the Functional Assessment of Chronic Illness Therapy (FACIT) - Fatigue scale [27] that evaluates self-reported fatigue level; (4) the Activities-specific Balance Confidence (ABC) Scale [28] that evaluates the self-reported confidence in activities of daily living; (5) the Short Physical Performance Battery (SPPB) [29,30] that objectively assesses lower extremity function including standing balance, gait speed, and ability to rise from a chair; and (6) the 6-Minute Walk Test (6MWT) [31] that evaluates walking endurance. *Physical fitness *will be assessed using (7) the body mass index based on the participants' height and weight measurement obtained by a standard medical weight scale. *Psychosocial-cognitive functions *will be assessed using (8) the Multidimensional Health Locus of Control (MHLC) Form C [32] for individuals' beliefs regarding where the control over their health lies; (9) the Center for Epidemiological Studies Depression (CES-D) [33] for depression; and (10) the Prospective Retrospective Memory Questionnaire (PRMQ) for short and long-term memory. *Physical activity *will be assessed using (11) the Rapid Assessment of Physical Activity [34]. *Physical activity *is also assessed based on the completed pedometer daily logs returned by all participants every four weeks.

#### Exercise group

*Exercise adherence *of the Exercise Group participants will be monitored by the exercise daily logs returned every four weeks, and phone surveys conducted by GRA2 every two weeks for the first 20 weeks and every four weeks for the rest of the study period. The phone surveys also monitor *exercise safety and progress*.

### Statistical analysis

#### Primary outcome variables

A mixed multiple analysis of variance (MANOVA) (Group X Time) will be conducted to determine if there is a significant interaction between the between- group (Group) and within-group (Time) comparisons for:

*Bone health *(bone mineral density) at baseline and 12-month follow-up session;

*HRQOL *(FACT-P and SF-36), and *physical function *(FACT-Fatigue, ABC, SPPB, and 6MWT) at baseline, 3, 6, 9, and 12-month follow-up sessions.

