#### Recruitment

A total of 60 patients will be consecutively recruited during the initial 3-months of the study from office visits at Cancer Care Manitoba. The attending physician will screen the patients for inclusion criteria (men aged 50 or older), diagnosed with prostate adenocarcinoma, will initiate and receive continuous ADT (LHRH alone or in combination with another anti-androgen for at least 12 months). If the patients meet the preliminary inclusion criteria, the physician will refer them to a clinical research nurse who will confirm that all inclusion and exclusion criteria are met, explain the study protocol, provide information sheet, and obtain written informed consent from any patients who would like to participate in the study. The clinical research nurse will provide a graduate research assistant (GRA1) with the signed consent forms and contact information of the patients who have agreed to participate in the study.

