#### Randomization of group assignment

GRA1 will be blinded to the group assignments of the participants. Therefore, after the baseline assessment and pedometer instruction, GRA2 will be responsible for the randomized group assignment. GRA2 will assign the participant the first available number from a randomly generated list consisting of "1" and "2". Number "1" is designated as the Exercise Group that will receive instructions in setting up an individualized 12-month home-based walking exercise program in addition to their daily activities. Number "2" is designated as the Control Group that will be advised to perform daily activities as usual and follow the standard medical advice from their attending physician.

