### Secondary outcome variables

A mixed MANOVA (Group X Time) will be conducted to determine if there is a significant interaction between the between-group (Group) and within-group (Time) comparisons for:

- *Physical fitness *(body composition) reflected in lean body mass at baseline and 12-month follow-up session;

*Physical fitness *(body mass index), *psychosocial-cognitive functions *(MHLC Form C, CES-D, and PRMQ), and *physical activity *(RAPA, daily step counts based on the pedometer daily logs) at baseline, 3, 6, 9, and 12-month follow-up sessions.

For the Exercise Group, Spearman-rank or Pearson product-moment correlation will be performed to determine if socio-demographic (age, marital status, living arrangement, education, and work status) and clinical factors (current cancer stage, time since diagnosis, treatment intent, testosterone level, Gleason score, comorbidity index, and PSA level) are associated with *exercise adherence *(average percentage of adherence to the target exercise frequency, duration and intensity based on the exercise daily logs) and *exercise safety *(occurrence rate of safety issues from the phone survey).

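### For the five-visit outcomes, the planned Group x Time MANOVA names no 12-month contrast, does not use baseline as a covariate, and can lose substantial power when the effect builds gradually

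*Protocol article*

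**What the plan says.** Under Statistical analysis, Primary outcome variables, the article states: "A mixed multiple analysis of variance (MANOVA) (Group X Time) will be conducted to determine if there is a significant interaction". This covers two sets of outcomes:

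- Bone health: "bone mineral density) at baseline and 12-month follow-up session".
- The quality-of-life questionnaires FACT-P and SF-36, together with four measures of physical functioning: "FACT-Fatigue, ABC, SPPB, and 6MWT) at baseline, 3, 6, 9, and 12-month follow-up sessions".

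Under Secondary outcome variables the rule is repeated: "A mixed MANOVA (Group X Time) will be conducted to determine if there is a significant interaction". There it applies to lean body mass at baseline and 12 months. It also applies to body mass index, MHLC, CES-D, PRMQ, RAPA and daily step counts at all five visits.

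Baseline is thus a level of Time. The text names no contrast at 12 months and no effect estimate. It does not say whether the outcomes are tested jointly or one at a time, or how missed visits are handled. On size, the Recruitment section says: "A total of 60 patients will be consecutively recruited during the initial 3-months of the study". The Methods call the study a pilot.

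**The concern.** The trial asks whether a 12-month walking programme helps men starting ADT. With five visits, a Group x Time interaction asks something else: whether the two mean profiles differ in shape at any time and in any direction. A significant result does not say when the arms differ or by how much, and it can come from an early difference that has gone by 12 months.

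The test also spreads its power over four contrasts per measure, or over 24 if the six measures are tested together (6 x 4). It does not use the correlation with baseline as ANCOVA does. In its classical form it needs a complete row of data per man, which matters with five sessions over a year and only 60 men. If less well or less adherent men miss more visits, an analysis of complete rows could be biased as well as small.

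**Working it through.** **Inputs.** From the article: 60 men, two arms, one baseline and four follow-up visits, six five-visit primary measures. Assumed, because the article gives no value: 30 per arm, two-sided alpha 0.05, effect size and shape, correlation between visits, and missed-visit rate. The article gives no power calculation to reproduce.

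**Formulas.**
- Interaction for one measure: Hotelling T-squared on the 4 changes from baseline. With n per arm, noncentrality = (n/2) x D², and df = 4 and 2n - 2 - 4 + 1. Under equal visit correlation r, D² is the sum of squared deviations of the five mean differences (0 at baseline) from their own mean, divided by 1 - r.
- 12-month ANCOVA: noncentral t, noncentrality = d / (√(1 - r²) x √(2/n)).

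**1. Effect rising linearly to 0.7 SD** (0, 0.175, 0.35, 0.525, 0.7; mean 0.35). Sum of squares = 2 x (0.35² + 0.175²) = 0.30625.
- r = 0.5: D² = 0.30625/0.5 = 0.6125; noncentrality 15 x 0.6125 = 9.19 on 4 and 55 df; power **63%**. ANCOVA: 0.7/(0.866 x 0.258) = 3.13; power **87%**.
- r = 0.7: D² = 0.30625/0.3 = 1.021; noncentrality 15.3; power **87%**. ANCOVA: 3.80; power **96%**.
- If all six measures are tested jointly, are affected equally and correlate 0.4 with each other, D² is multiplied by 6/(1 + 5 x 0.4) = 2, on 24 and 35 df. Power is 46% at r = 0.5 and 74% at r = 0.7.

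**2. Transient against sustained effect**, r = 0.5.
- 0.7 SD from 3 months on (0, 0.7, 0.7, 0.7, 0.7; mean 0.56): sum of squares 0.56² + 4 x 0.14² = 0.392.
- 0.7 SD at 3 months, 0.35 at 6, none at 9 and 12 (0, 0.7, 0.35, 0, 0; mean 0.21): 3 x 0.21² + 0.49² + 0.14² = 0.392.
- In both, D² = 0.392/0.5 = 0.784, noncentrality 11.76, power **75%**. The test gives a benefit that has vanished and one that lasts the same chance of significance.

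**3. Missed visits**, if complete rows are required and misses are independent.
- Men with all four follow-ups: 60 x 0.95⁴ = 49, 60 x 0.90⁴ = 39, 60 x 0.85⁴ = 31.
- At 10% per visit (about 20 complete per arm), linear effect, r = 0.5: 42% for one measure and 20% for the joint test, against 83% for ANCOVA on the 27 per arm seen at 12 months.

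**4. Other shapes and correlations.** For a constant 0.7 SD effect the interaction has 75% against 87% at r = 0.5, and 94% against 96% at r = 0.7. Under AR(1) with 0.8 per visit (baseline to 12 months 0.8⁴ = 0.41) it has **93% against 83%**, so the omnibus test wins. With the effect set so that ANCOVA has 80%, across equal correlations of 0.5 to 0.8 and AR(1) of 0.8 to 0.9, the single-measure interaction ranges from 42% to 97% on complete data. For a linear effect the range is 42% to 63%.

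**5. Bone density and lean mass.** With two time points, the interaction for one site or measure is the t-test on 12-month change. The ANCOVA-to-change variance ratio is (1 - r²)/(2 - 2r) = (1 + r)/2: 0.75 at r = 0.5, 0.85 at 0.7, 0.975 at 0.95. Where ANCOVA has 80% power, the change test has 68% at r = 0.5, 73% at 0.7 and 79% at 0.95.

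**The case against.** The strongest reply is that the size of the loss is a product of the assumptions. The article gives no effect size, correlation or dropout rate. The exercise protocol reaches its maintained level at around 18 to 20 weeks, so a plateau is as plausible as a straight line, and a plateau narrows or reverses the gap. Independent misses also favour ANCOVA: with monotone dropout, the men with incomplete rows are largely those missing at 12 months anyway. Nor is the comparison like for like. If six ANCOVAs were Bonferroni-adjusted (an assumed correction), power at r = 0.5 would fall from 87% to 65%, close to the 63% of one unadjusted interaction test. All of this stands, and it limits what can be claimed.

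A reader might infer several stronger points that the article does not support:

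- That the plan throws away most of the power. Most scenarios above do not show this, and some show a gain.
- That baseline is ignored. The interaction compares changes from baseline; only covariate adjustment is absent.
- That the 12-month difference is never tested. For each bone density site and for lean mass it is, and missed visits at 3, 6 or 9 months have no bearing on those comparisons.
- That the plan deletes men with a missed visit. Deletion is the default of the classical method, not stated text, and the full protocol or SAP, which is not shown, may handle it otherwise.
- That the trial is unblinded. It is single-blinded with a blinded assessor, although participants know their arm and several measures are self-reported.

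What the reply does not remove is the choice of test itself. The article specifies it, so this is not a detail left to another document.

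**Conclusion.** The point holds for the five-visit outcomes, primary and secondary. The named test does not estimate the 12-month effect, and in the worked example it gives a vanished and a lasting benefit the same 75% chance of significance; that does not depend on any claim about overall power. The power cost is conditional. With 30 per arm, equal visit correlation and a linear rise to 0.7 SD, it is 24 percentage points at r = 0.5 (87 - 63) and 9 at r = 0.7 (96 - 87). It is larger with missed visits under complete-row analysis, and it can turn into a gain under other effect shapes and correlations. For bone density and lean mass the test is adequate in aim, and the gain from ANCOVA is small if correlation with baseline is high. This is a worthwhile, low-cost improvement, not an error that invalidates the trial.

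**What to change.** - **Five-visit outcomes:** for each measure, fit a likelihood-based mixed model for repeated measures to the 3-, 6-, 9- and 12-month values. Use baseline value, group, visit and group x visit as fixed effects, with an unstructured covariance. Include every available follow-up visit, with men kept in their assigned group. Make the 12-month between-group difference with its 95% CI the main result.
- **Bone density and lean mass:** ANCOVA of the 12-month value on baseline and group.
- **Several primary comparisons:** state how they are prioritised or adjusted, or present them as pilot estimates with CIs and no confirmatory claim.

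The cost is the rewording of two paragraphs before analysis, with no new data. The single joint multivariate p-value is lost and replaced by several separate primary comparisons, which is why the third item belongs to the change. If those comparisons are formally adjusted, much of the power advantage may go; the interpretable 12-month estimate and the use of incomplete records remain.

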### Secondary outcome variables

A mixed MANOVA (Group X Time) will be conducted to determine if there is a significant interaction between the between-group (Group) and within-group (Time) comparisons for:

- *Physical fitness *(body composition) reflected in lean body mass at baseline and 12-month follow-up session;

*Physical fitness *(body mass index), *psychosocial-cognitive functions *(MHLC Form C, CES-D, and PRMQ), and *physical activity *(RAPA, daily step counts based on the pedometer daily logs) at baseline, 3, 6, 9, and 12-month follow-up sessions.

For the Exercise Group, Spearman-rank or Pearson product-moment correlation will be performed to determine if socio-demographic (age, marital status, living arrangement, education, and work status) and clinical factors (current cancer stage, time since diagnosis, treatment intent, testosterone level, Gleason score, comorbidity index, and PSA level) are associated with *exercise adherence *(average percentage of adherence to the target exercise frequency, duration and intensity based on the exercise daily logs) and *exercise safety *(occurrence rate of safety issues from the phone survey).

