### Baseline assessment session

GRA1 will contact the participants to schedule a baseline assessment. GRA1 will collect the socio-demographic and clinical characteristics, followed by primary outcome (HRQOL and physical function) and secondary outcome variables (physical fitness, psychosocial-cognitive functions, and physical activity).

GRA2 (another graduate research assistant) will provide each participant with a pedometer to monitor his ambulatory activities. The participants will be instructed to wear the pedometer during waking hours, except while bathing or swimming. The pedometer will be worn on a waistband, at or slightly anterior to the mid-axillary line. The exact location will be determined by a 50-step trial walk, and the placement that yields the least percentage error in step counts will be used for the individual's daily application. Pedometer daily logs, self-addressed envelopes, and extra batteries will be provided to all participants. At the end of each day, participants will record the date, total daily time wearing the pedometer, and the number of daily steps taken, and then reset the pedometer to zero. Every four weeks, GRA2, will call the participants to remind them to return their pedometer daily logs by mail in the self-addressed envelopes.

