The Exercise Group will follow a walking exercise program that comprises a progressive structured exercise protocol and progressive target daily step counts. The structured exercise protocol will initially begin with a 10-minute walking session, 3 sessions per week. The Exercise Group participants will be instructed to perform a 5-minute warm-up period by walking slowly prior to the 10-minute walking session. There will also be a 5-minute cool-down period by walking slowly, followed by a stretching routine after the 10-minute walking session. The stretching instruction sheet will be provided to the participants. GRA2 will also educate and demonstrate to the participants how the stretches are to be done. During the warm-up/cool-down periods, the participants will maintain an exertion level between 7.5 and 8 on the Borg Scale of Ratings of Perceived Exertion (RPE) [24] (i.e., extremely light level of exertion). During the 10-minute walking session, the participants will gradually increase the walking speeds until they attain and maintain an RPE level between 9 and 13 (i.e., very light to light exertion) according to their baseline physical activity level (sedentary, moderately active, or active) as reported on their self-reported physical activity questionnaire. Sedentary individuals will walk at RPE level 9 (very light exertion), moderately active individuals will walk at RPE level 11 (light exertion), and active individuals will exercise at RPE level 13 (somewhat hard exertion). Each participant's exercise level will be progressed every two week, first in frequency (1-day increment), then duration (5-minute increment), and lastly RPE level. Based on the set progression protocol, the Exercise Group participants will be performing five walking exercise sessions per week, 30 minutes walking per session, and will attain RPE level 15 (heavy exertion) during the walking session by around 18 to 20 weeks. This level of exercise protocol will be maintained for the rest of the study period. The participants are instructed to record the date, start time, exercise duration and maximum RPE attained during each session in an exercise daily log. The participants will also be encouraged to walk at their chosen pace at times outside their structured exercise protocol so as to achieve their assigned target daily step counts. The initial target will be set at 5,000 steps for sedentary individuals, 6000 steps for moderately active individuals, and 7,000 steps for active individuals. The target daily step counts will be progressed every two weeks (1000-steps increment) up to a maximum daily target of 10,000 steps. The participants will be counseled on the warning symptoms of impending cardiovascular events including chest pain or discomfort, shortness of breath, dizziness, severe headache, sudden onset of numbness or weakness, or calf pain suggestive of deep vein thrombosis. They will be strongly advised to discontinue the exercise program and report these symptoms to their attending physician and GRA2 immediately. An exercise advice and instructions sheet will be provided to the Exercise Group participants.

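### Daily step count is to be analysed from baseline, but the article describes no pedometer wear before group assignment

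*Protocol article*

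**What the plan says.** Under Secondary outcome variables, the protocol article states: "A mixed MANOVA (Group X Time) will be conducted to determine if there is a significant interaction". The outcomes in that test include "daily step counts based on the pedometer daily logs) at baseline, 3, 6, 9, and 12-month follow-up sessions".

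How the counts arise is set out under Baseline assessment session: "GRA2 (another graduate research assistant) will provide each participant with a pedometer to monitor his ambulatory activities". Before assignment the device is used only to find where it should be worn: "The exact location will be determined by a 50-step trial walk". Counting is then daily: "At the end of each day, participants will record the date, total daily time wearing the pedometer, and the number of daily steps taken". The logs are mailed back every four weeks.

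Under Randomization of group assignment, the order is "after the baseline assessment and pedometer instruction, GRA2 will be responsible for the randomized group assignment". Controls are told to carry on as usual. Exercise Group men enter the walking programme with a step goal: "The initial target will be set at 5,000 steps for sedentary individuals, 6000 steps for moderately active individuals, and 7,000 steps for active individuals". The goal rises by 1,000 steps every two weeks to a ceiling of 10,000. The Assessment sessions section allows one baseline session and then follow-up at 3, 6, 9 and 12 months.

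**The concern.** A Group by Time interaction reads the treatment effect as a difference between arms in change over time. That is sound only if the first time point precedes treatment in both arms. Here the article fixes two things that do not fit together: a baseline step count in the model, and a sequence in which the first full-day count comes after the device is issued, with assignment following the instruction in its use.

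If early log days stand in for baseline, the Exercise Group's starting value may already contain part of the programme's effect, and the interaction subtracts that part. If nothing is entered at baseline, the outcome has four time points and not the five stated.

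The outcome is secondary, but it matters for interpretation. The intervention is a walking programme with step goals, and pedometer steps are the only device-based comparison of walking between the arms. RAPA is a questionnaire, and the exercise logs and phone surveys cover one arm only. If the bone or function results are null, this measure helps to show whether walking actually differed.

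**Working it through.** There is no planned figure to reproduce: the article gives no expected step difference, standard deviation or power. The check has three parts.

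**1. Order of events.** Pedometer issued at the baseline session; placement found by a 50-step walk, which is not a daily count; first daily count written at the end of a day of wear; assignment after the instruction, with no interval stated. The randomisation and Exercise Group subsections sit within the Baseline assessment session, and no other visit before 3 months is listed. Activity categories come from a self-report questionnaire, which fits there being no measured baseline step count.

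**2. Share of the effect lost if early log days are used.** Let T be the initial target (5,000, 6,000 or 7,000, from the Exercise group protocol) and H a man's habitual steps before the programme, which the article does not give. Assume that men meet their targets exactly, controls stay at H, and the plateau is 10,000. Then

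lost share = (mean steps in the baseline window − H) / (10,000 − H).

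In week 1 the mean is T. Over the first four weeks it is (2T + 2(T + 1,000)) / 4 = T + 500.

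| T | H | Week 1 as baseline | First four-week log as baseline |
|---|---|---|---|
| 5,000 | 5,000 | 0 / 5,000 = 0% | 500 / 5,000 = 10% |
| 6,000 | 6,000 | 0 / 4,000 = 0% | 500 / 4,000 = 12.5% |
| 7,000 | 7,000 | 0 / 3,000 = 0% | 500 / 3,000 = 16.7% |
| 5,000 | 4,000 | 1,000 / 6,000 = 16.7% | 1,500 / 6,000 = 25% |
| 6,000 | 5,000 | 1,000 / 5,000 = 20% | 1,500 / 5,000 = 30% |
| 7,000 | 6,000 | 1,000 / 4,000 = 25% | 1,500 / 4,000 = 37.5% |

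For men further below target the loss grows. At 2,000 below it is 29% to 40% (week 1) or 36% to 50% (four weeks); at 3,000 below, 38% to 50% or 44% to 58%. In the other direction, a man already walking at or above T has no target-driven rise in week 1, and one at T + 1,000 or more has none in the first four weeks: the loss is then 0%.

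**3. What such a loss does to the test.** This is an illustration only. It assumes 30 men per arm (60 in total; no ratio is stated), a two-sided 5% level and a single change contrast in place of the MANOVA. The standardised effect with 80% power is √(2/30) × (1.96 + 0.842) = 0.723. With a lost share f, power = Φ(0.723 × √15 × (1 − f) − 1.96), where 0.723 × √15 = 2.80:

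- f = 10%: Φ(2.52 − 1.96) = Φ(0.56), about 71%.
- f = 25%: Φ(2.10 − 1.96) = Φ(0.14), about 56%.

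**The case against.** The strongest reply is that this is a journal article condensing a fuller protocol. No sentence says that assignment happens on the day the pedometer is issued, and none says which log days form the baseline. A wear period could exist elsewhere, and the exact window is a detail that an article commonly leaves out. This stands as a limit on confidence. It does not dispose of the point, because the article does state the order of issue, instruction and assignment, and separately states a baseline count in the model. The two conflict as written, and nothing shown hints at a run-in.

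A reader might go further and infer that no pre-randomisation count exists at all, and that the step result is biased towards zero. The documents do not support either as fact. The first rests on section order and visit count. The second needs two further conditions: that post-assignment days are used as baseline, and that the programme has already raised steps in those days. If no value is entered, the problem is a missing time point and not attenuation. If an early effect later fades, the interaction could even point the wrong way.

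Nor does the four-weekly return fix the window. It is a mailing schedule; the logs are dated by day, so a shorter window can be taken from them, and with the first days the loss can be nil. Finally, only one secondary outcome in a study described as a pilot is touched. RAPA and the other outcomes measured by GRA1 at the baseline session precede assignment, and delivery in the Exercise Group is also followed through exercise logs and phone surveys.

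**Conclusion.** The point holds in a limited form. On the sequence described, the baseline daily step count has no pre-assignment source. A value taken from the logs would be post-assignment and, in one arm, recorded under a step target; the interaction would then tend to understate the programme's effect on walking.

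The size cannot be fixed from the article. It is 0% if the first days are used and men already walk at or above their initial target, and about 10% to 38% if the first four-week log is used and men start at, or 1,000 steps below, that target and meet their targets. Larger shortfalls in habitual walking would raise it. If no baseline value is entered, the five-time-point analysis cannot be carried out for steps. Primary outcomes are unaffected. Confidence is moderate, because same-day assignment is inferred. The change is worth making because it costs nothing.

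**What to change.** State that no pedometer log kept after assignment serves as baseline. Compare daily step counts at 3, 6, 9 and 12 months between the arms as post-randomisation outcomes, adjusted for the RAPA score collected at the baseline session before assignment. The quantity of interest is then the between-group difference at those visits. The Group by Time interaction over the remaining four visits would show only whether that difference changes. Randomisation supplies comparability; RAPA adjustment is there for precision and does not stand in for a measured step baseline. Cost: analysis wording only.

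Optionally, if it can be done without an extra visit, collect a short pedometer log from every man before assignment and use it as baseline in both arms. This may not be cheap. The Exercise Group's screening and stretching demonstration come after assignment, so a later assignment could need another in-person contact beyond the five sessions. Follow-up is timed from ADT initiation, so a delay would also shorten time in the programme before the 3-month visit. If the full protocol already has a pre-assignment wear period, stating it and its window would settle the matter.

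### Pearson or Spearman correlation is fixed for three factors with no natural order; with three or more categories the result depends on how they are numbered

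*Protocol article*

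**What the plan says.** The last paragraph of the statistical section of the Protocol article (Secondary outcome variables) names the method and its scope, for the Exercise Group only: "Spearman-rank or Pearson product-moment correlation will be performed to determine if socio-demographic (age, marital status, living arrangement, education, and work status"). To these five socio-demographic factors it adds seven "clinical factors (current cancer stage, time since diagnosis, treatment intent, testosterone level, Gleason score, comorbidity index, and PSA level").

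There are two outcomes. Adherence is the "average percentage of adherence to the target exercise frequency, duration and intensity based on the exercise daily logs". Safety is the "occurrence rate of safety issues from the phone survey".

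The Data collection section lists the socio-demographic variables by name only: "Socio-demographic factors will include (1) age, (2) marital status, (3) ethnicity, (4) living arrangement, (5) education, (6) work status", followed by alcohol and smoking history. It does describe treatment intent as curative versus palliative, which is two-level. Neither section gives categories or coding for marital status, living arrangement or work status, or names a test other than the two correlations.

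**The concern.** Pearson correlation needs numeric values and Spearman correlation needs at least an order. Marital status (for example married, widowed, divorced, single) has neither, and the same holds for living arrangement and work status. To compute either coefficient, someone must attach numbers to the categories. With three or more categories, that choice decides the size of the coefficient, its sign and its p-value.

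This is more than a detail left to an analysis plan. The article fixes a method and lists the variables it applies to, and for three of them the two do not fit unless a two-level coding is added. An analysis plan that followed the text literally could carry the mismatch forward.

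At stake are the answers for 3 of the 12 factors, on which men adhere to the programme and which men have safety issues. That bears on feasibility, which the Discussion names in the study's objective.

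**Working it through.** The article states no number of tests, significance level or precision for this analysis, so there is no figure of its own to reproduce.

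**Count and analysis set**
- Factors: 5 + 7 = 12. Outcomes: 2. Associations: 12 × 2 = 24. If the three adherence components were analysed separately, there would be 4 outcomes and 12 × 4 = 48.
- Affected by the ordering problem: 3 factors × 2 outcomes = 6 of the 24.
- Men: the Recruitment section gives 60 in total, and only the Exercise Group is used. The allocation ratio is not stated. If it is 1:1, about 30 men are expected. Under simple randomisation the 95% range is 22 to 38 (Binomial(60, 0.5)), before dropout.

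**Does the numbering matter? A check by hand**

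Assumed values: four unordered categories A, B, C, D with 18, 4, 5 and 3 men, mean adherence 70, 55, 75 and 60, and within-category SD 12. Pearson r = Sxy / √(Sxx × Syy).
- Syy does not depend on the numbering. Between categories: 139,225 − 2,035²/30 = 1,184.2. Within: 30 × 12² = 4,320. Sum: 5,504.2.
- Numbering A=1, B=2, C=3, D=4: Sxx = 127 − 53²/30 = 33.37; Sxy = 3,545 − 53 × 2,035/30 = −50.17; r = −50.17 / √(33.37 × 5,504.2) = −0.12.
- Numbering A=3, B=1, C=4, D=2: Sxx = 258 − 84²/30 = 22.8; Sxy = 5,860 − 84 × 2,035/30 = 162; r = 162 / √(22.8 × 5,504.2) = +0.46.

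The men and outcomes are the same. With 30 men, |r| must exceed 0.36 for two-sided p < 0.05, so the first numbering shows no association and the second a nominally significant one of opposite sign.

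**All numberings of one simulated dataset**

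One dataset of 30 men was drawn from these assumed values, and both coefficients were computed under every numbering.

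| Coding of the factor | Pearson r | p | Spearman | p |
|---|---|---|---|---|
| Four categories, 24 numberings | −0.58 to +0.58 | 0.0008 to 0.70 | −0.54 to +0.54 | 0.002 to 0.57 |
| Three categories, 6 numberings | 0.24 to 0.54 in absolute size | 0.002 to 0.20 | 0.17 to 0.52 in absolute size | 0.003 to 0.38 |
| Two categories, 2 numberings | −0.43 or +0.43 | 0.018 both ways | −0.46 or +0.46 | 0.011 both ways |

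The symmetry about zero is automatic, because reversing a numbering reverses the sign. The informative part is the spread of absolute size and p-value.

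**The same data after the fix**

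Tests that ignore the labels give one answer each for the four-category factor: one-way ANOVA p = 0.009, Kruskal-Wallis p = 0.015.

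**The case against.** The strongest reply is that the defect depends on a coding the article does not give. If each factor is reduced to two levels, Pearson correlation is the point-biserial correlation, recoding changes only the sign, and the test is valid. Category definitions are often left to a fuller document. This stands as a condition on the point: the coefficients cannot be called meaningless outright. It does not remove the point, because the article names the correlations as the only method and says nothing of two levels for these factors.

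The illustration rests on assumed means, SD and category sizes and on a single draw. That also stands. It shows that the conclusion can change with the numbering; it does not forecast by how much in this trial.

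Three stronger readings are tempting, and the documents do not support them.
- A reader might infer that the analysis will probably name a false predictor. At a level of 0.05, 24 independent tests with no true association give 24 × 0.05 = 1.2 expected false positives and a chance of 1 − 0.95^24 = 71% of at least one. But the article states no significance level or decision rule for the correlations. The figure also needs independence and no true association anywhere. Factors such as stage, Gleason score and PSA plausibly overlap, and the same men supply both outcomes.
- A reader might infer that these correlations are meant to underpin the wellness programme. The Discussion says that of the study as a whole.
- A reader might infer that a correlation with the safety rate is wrong in itself. Rank correlation with an occurrence rate is legitimate, and a count model would be a preference.

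**Conclusion.** The point holds in conditional form. The article prescribes Spearman or Pearson correlation for marital status, living arrangement and work status, which have no natural order. If any of them is analysed with three or more categories, the coefficient and p-value depend on arbitrary numbering. In the illustrative four-category data this moved p between 0.0008 and 0.70. With two levels there is no defect.

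It concerns 6 of 24 associations. Age, time since diagnosis, testosterone and PSA are numeric, treatment intent is binary, and education, stage and Gleason score can be ordered, so the stated method can serve for them. About 30 men assumes 1:1 allocation.

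Severity is minor: the analysis is secondary, lies within one arm of what the Methods/Design section calls a pilot study, and leaves the randomised comparisons and the primary outcomes untouched.

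**What to change.** Change the wording of the last paragraph of the statistical section, or settle it in the analysis plan before the data are examined:
- For marital status, living arrangement and work status, use a Kruskal-Wallis test or one-way ANOVA. Alternatively, fix two levels in advance (for example partnered or not, living alone or not, working or not) and report the difference with its 95% CI.
- Keep Spearman or Pearson correlation for ordered, continuous and binary factors.
- Label the 24 associations as exploratory. False-discovery control across the set is optional.

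The cost is slightly more analysis work and, if categories are collapsed, some loss of detail. No new data, visits or participants are needed.
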